The authors intend to develop, implement, and evaluate the effectiveness of a theory-based integrated dengue education and learning (iDEAL) module in improving the KAP, environmental cleanliness index, and dengue index among schoolchildren in Selangor and Kuala Lumpur. The specific objectives are to develop the iDEAL module, determine and compare the baseline sociodemographic, socioeconomic, and dengue infection history between intervention and control groups, and evaluate the within- and between-group effects of the iDEAL module in improving the KAP, environmental index, and dengue index at baseline (T_0_), immediately (T_1_), one month (T_2_), and three months (T_3_) post-intervention.

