### Sample size estimation

The sample size was calculated based on the desired primary outcome, namely knowledge of dengue prevention and control. The sample size was calculated using the formula for testing the difference in proportions between two groups [20]. Adjustment for a 70% attrition rate established that the sample size required for this study is 800 pairs of intervention and control groups, which amount to 1600 participants.

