## Data analysis

The data analysis will involve the intention-to-treat analysis strategy. The approach analyses the results in a randomised study, where all randomised participants are included in the statistical analysis and analysed according to the group they were originally assigned, regardless of the treatment received.

The collected data will be analysed using IBM SPSS version 28 and descriptive and inferential statistics. Data exploration will be performed to identify data entry errors, missing data, and outliers. Subsequently, the numerical data will be identified as normally or non-normally distributed via statistical and graphical methods. The statistical method will involve calculating the skewness or standard error (SE) of skewness and the Kolmogorov-Smirnov parameter, while the graphical method will involve plotting and analysing histograms and stem and leaf box plots. Normally distributed data will be described using mean and standard deviation, while non-normally distributed data will be described using median and the first and third quartiles (Q1, Q3). Categorical data will be presented as frequency and percentage.

The hypothesis will be tested using a significance level with a p-value of 0.05 and a confidence interval of 95%. Results that yield a p-value < 0.05 will be considered statistically significant. For between-group comparisons, the mean difference of continuous and normally distributed data between the intervention and control groups will be compared using the independent sample *t*-test. For continuous but non-normally distributed data, the intervention and control groups will be compared using the Mann-Whitney U test. The frequency difference of categorical data between the intervention and control groups will be compared using the chi-square test. Fisher’s exact test will be used for data from 2 × 2 tables, which contain >20% cells with an expected count < 5.

Within-group changes over time will be compared using one-way repeated measure analysis of variance (ANOVA) for continuous and normally distributed variables. Cochran’s Q test will be used for within-group analysis of categorical data. The main effect and interaction between and within the intervention and control groups at T_0_, T_1_, T_2_, and T_3_ will be tested using the generalised linear mixed model (GLMM).

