## Ethics approval, trial registration, and consent to participate

The Universiti Putra Malaysia Ethics Committee for Research Involving Human Subjects approved this study (JKEUPM-2023-347, dated 19 June 2023). This study has also been approved for National Medical Research Registration of Malaysia (NMRR) registration on 25 September 2023 (NMRR ID-23-02823-PKM). Additionally, the Thai Clinical Trial Registry (TCTR) approved clinical trial registry registration (reference number: TCTR20230426009, dated 26 April 2023). This study protocol has been registered with the ClinicalTrials.gov committee (ClinicalTrials.gov Identifier: NCT05863026, dated 8 May 2023). Written approval from the MOE Malaysia regarding each selected school will be obtained before data collection. The relevant parties will be informed of all protocol changes. All participants will be informed that their enrolment will not affect their relationship with their teachers or school. The researcher will obtain written consent from each participant’s parent or caregiver. The participants will be issued a consent form upon agreeing to participate in the study before answering the baseline questionnaire. The participants will be allowed to withdraw at any point during the study.

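### Repeated-measures ANOVA and Cochran's Q drop any student who misses a visit (unless values are imputed), which does not fit the all-randomised rule; the GLMM already planned can supply the within-arm contrasts

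*Protocol article*

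**What the plan says.** The Introduction makes it a specific objective to "evaluate the within- and between-group effects of the iDEAL module in improving the KAP, environmental index, and dengue index" over T0, T1, T2 and T3.

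The Data analysis section gives four relevant statements:

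- Population: "all randomised participants are included in the statistical analysis and analysed according to the group they were originally assigned".
- Within-arm change, continuous outcomes: "Within-group changes over time will be compared using one-way repeated measure analysis of variance (ANOVA) for continuous and normally distributed variables".
- Within-arm change, categorical outcomes: "Cochran’s Q test will be used for within-group analysis of categorical data".
- Mixed model: "The main effect and interaction between and within the intervention and control groups" at the four time points will be tested with a GLMM.

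The software is SPSS. Missing data are to be identified during data exploration; the article does not say what is done with them.

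Two other sections show that incomplete follow-up is expected. The ethics section says "The participants will be allowed to withdraw at any point during the study". The Sample size estimation section says "Adjustment for a 70% attrition rate established that the sample size required for this study is 800 pairs of intervention and control groups", or 1600 participants in all.

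**The concern.** A one-way repeated-measures ANOVA and Cochran's Q are both computed on a complete row of values per student. In their standard form, a student who is absent on one assessment day, or who withdraws after T2, contributes nothing, although two or three assessments are on file. The article expects such students, says that all of them are included, and then names tests that leave them out.

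Two things are at stake. First, within-arm results could be reported under an intention-to-treat label when they describe only students who attended every assessment. Second, within-arm change is covered twice, by these tests and by the GLMM, on different sets of students. The two sets of results could differ for that reason alone, and the article does not say which governs.

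**Working it through.** **1. The plan's own figure.** The 800 per arm cannot be rebuilt, because the article gives no proportions, power or number before inflation. Working backwards with n / (1 - attrition):

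- 240 / (1 - 0.70) = 800, if 70% is attrition as written;
- 560 / (1 - 0.30) = 800, if 70% was meant as retention.

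**2. Students left in the two tests.** Complete students per arm = 800 × (1 - attrition), taking every student not lost as present at all four visits:

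| Attrition | Complete per arm | Complete in total |
|---|---|---|
| 70% (as written) | 240 | 480 |
| 30% (if 70% is retention) | 560 | 1120 |
| 20% (assumed) | 640 | 1280 |
| 10% (assumed) | 720 | 1440 |

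Occasional absence alone has a similar effect. If each of T1, T2 and T3 is missed independently with probability m, the complete share is (1 - m)³: 0.95³ = 0.857, 0.90³ = 0.729 and 0.80³ = 0.512, or about 686, 583 and 410 of 800.

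**3. Effect on the estimated change.** No figure in the article links dropout to score, so every parameter here is an assumption. Inputs: 400,000 simulated students in one arm; means 0, 0.5, 0.4 and 0.3 SD at T0 to T3 (true T0-to-T3 change 0.30 SD); correlation 0.5 between visits; permanent dropout, with lower scorers at the previous visit more likely to leave, at log-odds 0.5 to 1 per SD.

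| Loss per interval | Students complete | Change in completers | Understatement |
|---|---|---|---|
| 5% | 86% | 0.29 to 0.28 SD | 4 to 8% |
| 10% | 73% | 0.28 to 0.26 SD | 7 to 14% |
| 20% | 51% | 0.25 to 0.22 SD | 16 to 25% |

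Repeat runs agree to within about 0.01 SD. Two variations matter:

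- Dropout unrelated to score: the completer change is 0.30 SD at all three loss rates, so there is no bias.
- Correlation 0.7 instead of 0.5: the harshest case (20% loss, log-odds 1) gives about 0.256 SD, and (0.30 - 0.256) / 0.30 is about 15% rather than 25%.

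**4. Does the planned type of model avoid this?** A second simulation fitted a likelihood mixed model: 15 runs of 800 students in one arm, the same mean profile, random-intercept and residual SD both 0.7, and dropout depending on the previous score. Completers, about 548 of 800, gave 0.24 against a true 0.30. The mixed model on all available visits kept all 800 students and gave 0.30.

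These runs cover continuous scores and permanent dropout. The Cochran's Q half and intermittent absence were not simulated; for those, the point rests on who is excluded.

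**The case against.** The strongest reply is the sentence that follows the two tests. The GLMM is assigned to effects within as well as between the groups, and it can keep students with partial follow-up. A reader might infer that the within-arm objective is answered in completers only. The article does not support that: the objective is also served by the GLMM, and the conflict is confined to the two named tests. Nor does it reach the between-arm GLMM comparison, which carries the hypothesis that the intervention group improves more than the control group.

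Second, imputation before the two tests would remove the exclusion. Rules for missing data may stand in a full protocol or analysis plan that is not shown, so their absence from an article is no fault. This stands, and it makes the point conditional. It does not remove it, because the article itself fixes both the tests and the inclusion rule, and the two fit together only if something further is added.

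Third, intention to treat chiefly protects the randomised comparison, and a before-after test within one arm is not one. That limits the consequences. But the article words its rule as one about who is included in the analysis, without confining it to the between-arm comparison.

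Fourth, bias is not certain. It needs dropout related to score, which no section states. This stands, and the range must start at zero.

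**Conclusion.** The point holds in limited form. Unless missing values are imputed, repeated-measures ANOVA and Cochran's Q are completer analyses and do not fit the article's statement that all randomised participants are included. On the article's own attrition figure they could rest on as few as 240 of 800 students per arm, or 560 if the figure meant retention; that ambiguity cannot be settled from the document.

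Precision is lost whenever visits are missed. Bias depends on the assumed dropout: none if it is unrelated to score, and 4 to 25% understatement of a 0.30 SD change under the score-dependent patterns with correlation 0.5. These figures show direction and plausible size and are not a forecast. The simulated mixed model recovered the true change because dropout depended only on scores already observed; that protection would not extend to dropout driven by unobserved scores.

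**What to change.** In the Data analysis section, and in the matching sentences of the Abstract, replace repeated-measures ANOVA and Cochran's Q with within-arm time contrasts (T1-T0, T2-T0 and T3-T0) taken from the GLMM already planned, using all available assessments. If the two tests are kept, label them as supplementary completer analyses and state that the GLMM contrasts govern if the two disagree.

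The cost is a change of analysis wording. The model is already planned in the same software, and no further data or visits are needed.

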### Allocation concealment

A randomisation list will be generated using “Create a block randomisation list” (Sealed Envelope Ltd., 2019). The main investigator will conduct the sequence generation and allocation concealment. Trained researchers will implement the study, which includes participant enrolment, envelope opening, and intervention administration in accordance with the CONSORT statement [21]. The list will include unique software-generated allocation codes consisting of two letters, followed by ≥ 1 digits (BW2, AM4, AB1, etc.). The codes will represent the intervention or control group. Only the sequence generator will be aware of the meaning of the codes to ensure allocation concealment. Subsequently, participants will be recruited using sequentially numbered, opaque, and sealed envelopes. The codes will be printed, cut out, and sealed in opaque envelopes. Subsequently, the envelopes containing the randomisation codes will be drawn by the liaison officer at each participating school. The randomisation codes will be released after schools are recruited for the study, which would occur following the completion of the baseline measurement. Thus, the parties involved during the randomisation will be blinded to the group to which the schools will be allocated before the codes are revealed.

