## Data collection

Upon initiating the study, the liaison officer will obtain consent from the students who fulfil the eligibility criteria. Subsequently, T_0_ data will be obtained from the students who consent to participate in the study. The participants allocated to the intervention group will be given appointments within one month for intervention package delivery according to class. The total duration of the intervention sessions will be approximately 30 minutes in three meetings. After completing the intervention, the participants will be required to answer the post-intervention assessment measuring the study outcome at T_1_, T_2_, and T_3_. The control group will undergo the same assessment as the intervention group at T_0_, T_1_, T_2_, and T_3_. Fig 3 depicts the study flow diagram based on the CONSORT 2010 statement [20].

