## Strengths and limitations

This study will involve a systematic intervention module development that includes a literature review, need assessment for the relevant target population, and SME. This approach influences the intended outcome and ensures an effective end product. The risk of contamination will be minimised via cluster randomisation. Ensuring that the selected schools are 10 km away from each other would further minimise the contamination risk. Thus, the intervention module effect on the intended outcome can be precisely measured.

Although the module development, implementation, and effectiveness assessment measures in this study are robust, the intended KAP outcome measurements will be self-reported. A self-administered questionnaire remains an appropriate measurement in a community intervention study focusing on the individual influence on KAP. Additionally, the researcher will measure the environmental cleanliness index and dengue index, which will provide reliable and valid measurements.

One possible challenge in this study is limited enrolment. In this instance, the researchers will adjust the recruitment methods, extend the enrolment periods, and cooperate with other research institutions. Education, regular contact, reminders, support services, and incentives increase participant adherence. Pre-defined assessment, reporting, and intervention protocols will be established in the case of concurrent events. The effects of such events on the study will be monitored, documented, and evaluated.

The intervention and control groups might experience prevention and control activities by health authorities whenever the school experiences a dengue outbreak. Considering that these activities are part of the standard care that both groups could receive during the study period, this condition will be controlled during analysis and interpretation. Information on these activities will be collected from both groups. The research outcomes based on this condition will be carefully interpreted.

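### The planned mixed model counts the pre-allocation visit T0 as an outcome, so its group main effect over T0 to T3 is not the module's effect; name a T0-adjusted arm difference instead

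*Protocol article*

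**What the plan says.** The Data analysis section of the protocol article states that "The main effect and interaction between and within the intervention and control groups at" T0, T1, T2 and T3 will be tested with the GLMM. This makes T0 one of four levels of the outcome and names two kinds of term, a main effect and an interaction. The section sets one 0.05 significance level and does not tie the hypothesis to either term. The Introduction takes the same view of T0, since the objective is to "evaluate the within- and between-group effects of the iDEAL module in improving the KAP, environmental index, and dengue index at baseline" and at the three later visits.

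The Allocation concealment section places T0 before allocation is known: the codes are released after schools are recruited, "which would occur following the completion of the baseline measurement". The Data collection section has both arms measured at all four visits ("The control group will undergo the same assessment as the intervention group at" T0 to T3), with the intervention delivered after T0.

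Separately, the Strengths and limitations section expects that both arms may experience "prevention and control activities by health authorities whenever the school experiences a dengue outbreak". It says that "these activities are part of the standard care that both groups could receive during the study period" and that "this condition will be controlled during analysis and interpretation". Information on the activities will be collected in both groups, and results are to be interpreted with care.

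**The concern.** No module effect can exist at T0. A group main effect averaged over all four visits therefore mixes one difference that is zero by design with three that may be real. If that term is read as the module's effect, it understates it. If the software uses T0 as the reference level, the coefficient labelled group holds no treatment effect at all.

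The interaction is the term that carries the effect. The overall group-by-time test, however, asks whether any of three contrasts differs from zero and returns no single estimate with a confidence interval. Change from T0 also uses the baseline score less efficiently than covariate adjustment does.

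A smaller, conditional worry concerns outbreak activity. It arises after allocation and is triggered by dengue at the school, and the dengue index is itself a trial outcome. Adjusting the treatment comparison for something that allocation may change would no longer estimate the module's total effect.

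**Working it through.** **Inputs.** From the article: four visits, one before and three after allocation; 1:1 allocation; 40 schools; 1600 pupils, hence 40 per school (1600/40). The article gives no figure for the GLMM group effect, so there is none to reproduce. It gives no effect size, power, intraclass correlation or within-pupil correlation either. Those used below are assumptions.

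**1. What the group main effect estimates.** Let the arm differences at T0 to T3 be 0, d1, d2, d3. With equal visit weights:

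main effect = (0 + d1 + d2 + d3)/4

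- Constant effect d: 3d/4 = 0.75d, a 25% dilution.
- Effect at T1 only: d1/4 = 0.25 of the T1 effect.
- T0 as reference level: the group coefficient is the T0 difference, with expectation 0.

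**2. What the interaction estimates.** The contrast (mean of T1 to T3) minus T0 is (d + d + d)/3 - 0 = d, with no dilution.

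**3. Simulation check of steps 1 and 2.** 40 schools of 40 pupils, assumed intraclass correlation 0.05, within-pupil correlation 0.5, constant effect 0.30 SD, 4000 runs. The main effect averaged 0.22 (expected 0.75 x 0.30 = 0.225), the interaction contrast 0.30, and the T0 difference between -0.003 and 0.001.

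**4. What T0 adjustment is worth.** Assume a continuous score with unit variance, equal correlation r between all visits, complete data and no school variance. Per-pupil variances:

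- one visit: 1 unadjusted, 1 - r^2 adjusted for T0;
- mean of T1 to T3: (1 + 2r)/3 unadjusted, (1 + 2r)/3 - r^2 adjusted;
- change (mean of T1 to T3 minus T0): (1 + 2r)/3 + 1 - 2r = 4(1 - r)/3.

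A ratio of variances is a ratio of sample sizes.

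| r | one visit: 1/(1 - r^2) | mean, unadjusted | mean, adjusted | change | unadjusted/adjusted mean | change/adjusted mean |
|---|---|---|---|---|---|---|
| 0.3 | 1.10 | 0.533 | 0.443 | 0.933 | 1.2 | 2.1 |
| 0.5 | 1.33 | 0.667 | 0.417 | 0.667 | 1.6 | 1.6 |
| 0.7 | 1.96 | 0.800 | 0.310 | 0.400 | 2.6 | 1.3 |

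The change variance exceeds the adjusted variance by (1 - r)^2 (at r = 0.5: 0.667 - 0.417 = 0.25). For the T1 to T3 mean, covariate adjustment is therefore better at every r below 1.

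**5. Outbreak activity.** The same simulation, with activity assumed to raise scores by 0.2 SD. If allocation does not change activity, the T1 to T3 estimate is 0.30 with or without adjustment. If the module lowers the log-odds of activity by 1, the total effect is about 0.26. The adjusted estimate is then 0.27, 0.30 or 0.33, depending on how unmeasured school risk relates to activity.

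**The case against.** The strongest reply is that a repeated-measures model with group, time and group-by-time terms, including T0, is standard. The same sentence that names the main effect also names the interaction, and the contrasts against T0 recover the full effect. That stands. A reader might infer that the trial will report an effect 25% too small, but the article nowhere says that the pooled main effect will be presented as the module's effect. The dilution applies only if it is used that way. The choice of deciding term and of a baseline covariate may also sit in an analysis plan that is not shown. What remains is stated in the article itself: T0 is a pre-allocation outcome level, and a main effect over T0 to T3 is tested.

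A reader might also infer that the main effect always costs much power. That depends on the comparator. Under the step 4 assumptions, suppose the T0-adjusted T1 to T3 mean has 80% power. The main effect then has 53%, 40% and 26%, and the 3-df interaction 34%, 43% and 52%, at r = 0.3, 0.5 and 0.7. If instead a T0-adjusted single visit has 80%, the main effect has 83%, 63% and 40%, and the 3-df interaction 63%, 70% and 76%. At r = 0.3 the main effect is then slightly the more powerful. A 1-df change contrast over T1 to T3 has 79%, 84% and 89% on that benchmark, so it beats the single visit at r = 0.5 and 0.7. A general claim of lost power is therefore not supported.

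On outbreak activity, the article names no covariate and does not mention the GLMM in that place. It also promises careful interpretation.

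**Conclusion.** The point holds in limited form. The pooled group main effect over T0 to T3 is not the treatment effect. It is 0.75 of an effect constant over T1 to T3 (this needs only equal visit weights), 0.25 of one confined to T1, and nothing but chance imbalance under T0 reference coding. The interaction contrasts are valid and undiluted, so the model is not invalid. Its weaknesses are that the overall 3-df test gives no single estimate and that change from T0 is less efficient than adjusting the same T1 to T3 mean for T0.

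The gains from adjustment (1.1 to 2.0 times the sample for one visit, 1.2 to 2.6 for the T1 to T3 mean) are illustrative. They rest on assumed correlations, compound symmetry, complete data, a continuous score and no school variance, whereas the trial randomises 40 schools.

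The outbreak point is conditional. A reader might infer that the planned control will bias the result. The documents do not show this: distortion arises only if allocation changes outbreak activity, and in the simulation it ran from almost nil to upward. Such a change is plausible, because the article hopes to lower the dengue index and dengue risk, but it is not established.

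**What to change.** For the pupil-level KAP scores, state that T1, T2 and T3 are the outcomes. Use fixed effects for arm, visit, arm-by-visit, T0 score and school level (primary or secondary), and random intercepts for school and pupil. A model that keeps T0 as an outcome but constrains the arms to a common baseline mean is an acceptable alternative. Name one baseline-adjusted arm difference as the treatment effect, either the T1 to T3 mean or a single specified visit, and attach the 0.05 test and 95% interval to it. State that the pooled main effect over T0 to T3 will not be interpreted as the module's effect.

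Keep outbreak-triggered activity out of the primary model. Report it by arm, and show an adjusted result only as a labelled sensitivity analysis.

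The cost is wording. T0 scores, school level and information on outbreak activity are already to be collected, so no visit, instrument or pupil is added.

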### Study population

The Ministry of Education (MOE) Malaysia will supervise this study. The participants will be Standard 4 and Form 4 students from primary and secondary government schools, respectively, in Selangor and Kuala Lumpur. There are 661 primary schools and 279 secondary schools in Selangor, and 218 primary schools and 125 secondary schools in Kuala Lumpur. The schools include national, technical, science, religious, and boarding schools [19].

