### Sampling method and participant recruitment

This study will use multistage sampling. The first sampling stage will use proportionate simple random sampling to select 40 schools based on the Selangor and Kuala Lumpur districts. There are nine districts in Selangor and 11 districts in Kuala Lumpur. Thus, all 20 districts in Kuala Lumpur and Selangor will be included for the proportionate simple random sampling to select 40 schools. The school selection sampling frame will be the list of Selangor and Kuala Lumpur schools according to primary and secondary schools from 20 districts. For this exercise, the sampling frame A will consist of primary school while sampling frame B will consist secondary school. This sampling frame to ensure the required 20 schools for Standard 4 (primary school) and 20 school from Form 4 (secondary school) can be obtained. In the second sampling stage, one classroom from each school selected from the first sampling stage will be chosen using simple random sampling. These samplings will yield 20 Standard 4 classrooms and 20 Form 4 classrooms. Subsequently, the sampling frame will be the Standard 4 and Form 4 classroom list from each selected school. All students in the selected classrooms will be invited to participate in the study.

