### Randomisation

School cluster randomisation will be used to ensure administrative efficacy, reduce risk of experimental contamination, and enhance participant compliance. The Standard 4 and Form 4 classrooms will be randomly divided into intervention and control groups. The randomisation unit will be 1:1 in the control or intervention group. Contamination due to geographical issues will be minimised by setting the distance between each school to a minimum of 10-km radius from each other. A school will be randomly reselected from the sample frame to replace any school that does not fulfil this criterion.

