### Sequence generation

Upon recruiting the schools and participants that fulfil the eligibility criteria, schools will be allocated to intervention or control groups using permuted block randomisation. The approach will ensure that closely balanced numbers of schools will be allocated to each study arm. Variable block sizes of 4, 6, and 8 will be used to blind the researcher from predicting the school allocation process.

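### Level of schooling (primary or secondary) is a sampling stratum but is not used in the stated allocation or arm comparisons, which costs precision at single time points and can hide a level-specific effect

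*Protocol article*

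**What the plan says.** Sampling (Protocol article, Sampling method and participant recruitment): "the sampling frame A will consist of primary school while sampling frame B will consist secondary school". The result is fixed by design: "These samplings will yield 20 Standard 4 classrooms and 20 Form 4 classrooms".

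Allocation (Randomisation; Sequence generation): "The Standard 4 and Form 4 classrooms will be randomly divided into intervention and control groups", in a 1:1 ratio, and "schools will be allocated to intervention or control groups using permuted block randomisation", with block sizes of 4, 6 and 8. Neither section says that the blocks are run separately for primary and secondary schools.

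Analysis (Data analysis): intervention and control are compared by independent-sample t-test, Mann-Whitney U test, or chi-square/Fisher's exact test, depending on the type of data. The GLMM is then used to test the "main effect and interaction between and within the intervention and control groups" at T0, T1, T2 and T3. Level of schooling is not named there as a factor, covariate, interaction or subgroup. The specific objectives in the Introduction do not name it either.

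**The concern.** Standard 4 and Form 4 pupils are at very different stages of schooling, and the protocol describes one knowledge, attitude and practice questionnaire for both. A difference in mean score between the levels is to be expected, and the level of every school is known before the trial starts. Leaving a known, probably prognostic stratum out of the arm comparison has two consequences.

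- **Precision.** The difference between levels is counted as variation between schools. If allocation is not balanced within level, a chance excess of one level in one arm also shifts the estimate itself.
- **Interpretation.** One module is to be promoted for school use nationwide (Data sharing section). If it works at one level only, a single pooled effect would not show this.

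**Working it through.** **Inputs from the protocol.** 40 schools, 20 per level, one class per school, 1:1 allocation, 1600 pupils. This gives 20 schools per arm and 1600/40 = 40 pupils per class. The stated 800 per arm cannot be reproduced, because the two proportions and the power are not given. Nothing below depends on that.

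**Assumptions, not in the protocol.** Within-level SD 1; ICC 0.05 (range 0.02 to 0.10); primary-secondary gap g of 0.3 to 1.0 SD; true effect 0.25 SD; two-sided 5% test; analysis of school means at one time point; unstratified allocation.

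**Step 1, variance of a school mean.**
- Within level: ICC + (1 − ICC)/40 = 0.05 + 0.95/40 = 0.07375.
- With level ignored and half the schools at each level, add g²/4.

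**Step 2, arm difference.** SE = √(2 × variance/20). Power is from the noncentral t distribution, with 37 df with the level term and 38 df without it.

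| g (SD) | variance of school mean | ratio to 0.07375 | SE | power at 0.25 SD |
|---|---|---|---|---|
| level in the model | 0.07375 | 1.00 | 0.086 | 81% |
| 0.3, level omitted | 0.09625 | 1.31 | 0.098 | 70% |
| 0.5, level omitted | 0.13625 | 1.85 | 0.117 | 55% |
| 1.0, level omitted | 0.32375 | 4.39 | 0.180 | 27% |

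Across ICC 0.02 to 0.10 and g 0.3 to 1.0, the ratio runs from 1.18 (ICC 0.10, g 0.3) to 6.62 (ICC 0.02, g 1.0).

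**Step 3, chance imbalance.** Treat unstratified allocation as 20 schools drawn at random from 40 (hypergeometric, an approximation to permuted blocks). The chance that the levels split 12:8 or worse within an arm is 34%; for 13:7 or worse it is 11%. A 12:8 split with g = 0.5 shifts the unadjusted arm difference by (12/20 − 8/20) × 0.5 = 0.10 SD, which is 0.10/0.25 = 40% of the assumed effect.

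**Step 4, change from T0.** A gap that stays constant cancels. In a simulation with ICC 0.05 and g = 0.8 (4000 runs), the SE of the contrast in change was 0.066 without the level term and 0.067 with it. If the gap shifts by 0.2 SD between the two time points, the SEs were 0.074 and 0.068.

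**Step 5, effects that differ by level.** With assumed effects of 0.40 SD (primary) and 0.10 SD (secondary), the pooled effect is (0.40 + 0.10)/2 = 0.25 SD. Equal effects of 0.25 SD in both levels give the same pooled figure, so it cannot tell the two situations apart.

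**The case against.** **Silence is not exclusion.** The GLMM sentence says which effects will be tested; it does not list every model term. The Strengths and limitations section says that outbreak control activities will be controlled for, yet Data analysis names no term for them, so that section is evidently not a full covariate list. An article may leave such a list to a fuller plan. This stands for the GLMM: one cannot say that the protocol rules the term out. It does not cover the between-group tests, which are named and cannot take a covariate.

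**The longitudinal contrast is hardly touched.** This also stands. Step 4 shows almost no loss in the group-by-time contrast when the gap is constant. The loss belongs to single-time-point comparisons and to the group main effect.

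**The size depends on allocation and on the unit of analysis.** A reader might infer that the loss is the same however schools are allocated. It is not. With 10 schools of each level per arm, the gap cancels from the arm difference, and only the estimated SE of an unadjusted analysis is too wide. In a pupil-level t-test the estimated variance would rise by only 1 + g²/4, that is 1.06 at 0.5 SD and 1.25 at 1.0 SD, or intervals about 3% and 12% wider. Under unstratified allocation, that same test would leave the chance imbalance largely unaccounted for.

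**The pooled effect is not meaningless.** A reader might infer that the pooled effect describes neither level, or that its 50:50 mix is wrong because "There are 661 primary schools and 279 secondary schools in Selangor, and 218 primary schools and 125 secondary schools in Kuala Lumpur", so that 879 of 1283 schools (68.5%) are primary. The protocol does not support either reading. If the effect is the same at both levels, the pooled figure describes both; if not, it is still a valid equal-weight average. The counts are of schools, not of Standard 4 and Form 4 pupils, and the protocol promises no population-weighted estimate. There is no basis for asking for reweighting.

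**Conclusion.** The point holds in limited form. Level of schooling is built into the sampling but is absent from the stated allocation, from the two-sample tests and from the effects named for the GLMM. The loss can be material for comparisons at one time point and for the group main effect: a variance ratio of 1.31 to 4.39 for gaps of 0.3 to 1.0 SD at ICC 0.05, and 55% against 81% power at a 0.5 SD gap. These figures rest on an assumed gap, ICC and effect, a within-level SD of 1, unstratified allocation and analysis by school. They do not carry over to the group-by-time contrast under a constant gap. Separately, no stated analysis would show whether the module's effect differs between Standard 4 and Form 4. The plan should be changed because the remedy uses information already held, but this does not invalidate the trial.

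**What to change.** In Data analysis:

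1. Base the arm comparisons on the GLMM instead of the separate two-sample tests, with level of schooling (primary/secondary) as a fixed effect. Word it this way so that it is not mistaken for the random effect for school, which is a different matter.
2. Pre-specify the group-by-time-by-level interaction, with its lower-order terms.
3. Report the effect with its 95% CI for each level as well as overall.
4. Label the level-specific estimates as less precise. With about 10 schools per arm at each level, SE = √(2 × 0.07375/10) = 0.121 at ICC 0.05, so power for 0.25 SD is only about one half (54% by the normal approximation). A non-significant result at one level must not be read as absence of effect.

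Cost: a few sentences in the plan, one degree of freedom for level (38 to 37 in the school-level calculation) and a little more analysis. No new data are needed. The change is worth making however the schools are allocated, although the size of the gain depends on that.
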